### Data Management

StudyTrax (v3.0.0103), a web-based electronic data capture software, will be developed to house case report forms for data collected throughout the study. Case report forms will be developed to include field-specific validation code, procedures to check data ranges, and reminders to enter required data to ensure data integrity. Research staff utilizing the database will be provided role-specific privileges to the database. Two members of the study staff will perform double data entry on all clinical measures. Dietary data will be collected using the Nutrition Data System for Research (NDSR) database. Physical activity data will be collected on case report forms designed in Microsoft Access.

### Quantitative Evaluation: Analytic Plan

#### Sample Size and Power Calculations

As a comparative effectiveness study, patients in both arms will receive interventions potentially resulting in improvements in the primary outcomes. Hence, a very large sample size would be required to demonstrate either statistically significant comparative effectiveness or superiority of one group over the other. As a result, and in recognition of the project’s status as a feasibility study, the study was powered to be able to demonstrate within group improvements in one of the key outcomes: physical activity. A sample size of 47 was determined to be sufficient to show a within group improvement, from pre- to post-, of 20% of the sample from inactive to moderate intensity physical activity, with a power of 80% at 0.05% level of significance.

#### Analysis and Statistical Tests

Our null hypothesis is that there will be no significant differences in outcome measures between the VW and face-to-face conditions. We will test this null hypothesis against the alternative that the VW condition is not as effective as face-to-face intervention using a two-sample Kolmogorov-Smirnov test for changes distributions of A1c. In other words, the VW intervention will be as good as or better than face-to-face intervention in decreasing A1c. The *P* values will be calculated using binomial tests for proportions and *t* tests for continuous variables. We will use RStudio (version 0.96.330) [28] for statistical analysis.

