**Results:**

The primary outcomes of interest are feasibility of the VW intervention and its potential efficacy on glucose control and diabetes self-management behaviors, compared to the face-to-face condition. Analysis will use a two-sample Kolmogorov-Smirnov test for changes in variable distribution. *P* values will be calculated using binomial tests for proportions and *t* tests for continuous variables.

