### Hypothesis

We hypothesize that the VW-based experimental intervention condition will produce outcomes related to feasibility and potential efficacy that are comparable or greater than those observed in the face-to-face control condition.

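### The protocol tests a directional A1c alternative with a Kolmogorov-Smirnov test whose side is not stated, and leaves unclear whether that test or a t test decides the A1c comparison

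*Protocol article*

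**What the plan says.** The protocol article, under Analysis and Statistical Tests, gives the null as "Our null hypothesis is that there will be no significant differences in outcome measures between the VW and face-to-face conditions". It tests this "against the alternative that the VW condition is not as effective as face-to-face intervention", "using a two-sample Kolmogorov-Smirnov test for changes distributions of A1c". The next sentence restates the aim: "the VW intervention will be as good as or better than face-to-face intervention in decreasing A1c". The sentence after that says that P "values will be calculated using binomial tests for proportions and" t "tests for continuous variables. We will use RStudio" for the computation. A1c is not excepted from the t-test rule, and the Kolmogorov-Smirnov (K-S) test is not called one-sided or two-sided.

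The Abstract (Results) is looser: "Analysis will use a two-sample Kolmogorov-Smirnov test for changes in variable distribution". It gives no direction, does not tie the test to A1c, and repeats the rule on binomial and t tests. The Hypothesis section expects VW outcomes "comparable or greater than those observed in the face-to-face control condition". Outcomes and Study Measures places glucose control among the primary outcomes, as a between-group comparison of change from baseline to 4 months.

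**The concern.** Whether VW lowers A1c less than face-to-face is a question about location and direction. A two-sided K-S test asks whether the two distributions of change differ in any way. It can reject because VW is worse, because VW is better, or because one arm is more variable. A significant result therefore does not by itself support the stated alternative.

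The K-S statistic is the largest gap between two cumulative curves. It is not a difference in A1c and has no confidence interval on the A1c scale, although an estimate with its uncertainty is what a pilot hands to a larger trial.

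Because the t-test rule may or may not include A1c, a primary outcome has no clearly designated deciding analysis.

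**Working it through.** **No planned figure to reproduce.** The only sample-size figure, 47, is for a within-group change in physical activity. It does not bear on the A1c comparison.

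**Inputs.** From the protocol: 100 women in two arms and block size 4, so about 50 per arm if allocation is 1:1; 47 serves as a second, smaller arm size. Assumed, because the protocol gives none: SD of A1c change 1.5, true difference 0.5 percentage points (0.5/1.5 = 0.33 SD), normal changes, no dropout, 5% level. Unequal-spread case: equal means, SDs 1.5 and 2.5.

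**Critical values.** With n per arm, the exact one-sided K-S tail is P(D⁺ ≥ k/n) = C(2n, n−k)/C(2n, n). The two-sided tail follows from the corresponding alternating sum.

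- n = 47: two-sided k = 14 (actual size 3.0%), one-sided k = 12 (4.7%).
- n = 50: two-sided k = 14 (3.9%), one-sided k = 13 (3.4%).

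**Rejection rates** (40,000 simulated trials per case; the one-sided test looks for VW worse):

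| True state | K-S two-sided, 47 / 50 | K-S one-sided, 47 / 50 | t test two-sided, 47 / 50 |
|---|---|---|---|
| VW worse by 0.5 | 22% / 26% | 39% / 34% | 36% / 37% |
| VW better by 0.5 | 21% / 26% | 0.1% / 0.1% | 36% / 38% |
| Equal means, SDs 1.5 and 2.5 | 14% / 19% | 18% / 15% | 5% / 5% |

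Formula check on the t test at 50 per arm: 0.333 × √(50/2) = 1.67, and Φ(1.67 − 1.96) = Φ(−0.29) ≈ 39%, close to the simulated 37% to 38%.

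**Reading the table.**

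1. *Direction.* The two-sided K-S test rejects equally often, apart from simulation error, whether VW is worse or better. The one-sided form removes this problem.
2. *Spread.* Neither form is confined to average change: both reject well above 5% when means are equal and only the spread differs.
3. *Power.* With normal changes, two-sided K-S has 22% to 26% against 36% to 38% for the t test. The ranking depends on shape. At a shift of 0.5 SD and 50 per arm, K-S against t is 53% against 70% with normal errors, 75% against 71% with t(4) errors, and 83% against 71% with Laplace errors.
4. *Two tests.* With no true difference, counting either the two-sided K-S or the t test as significant rejects in about 6% to 6.5% of trials. At a true difference of 0.5 the two tests disagree in 18% to 19%.
5. *Non-rejection.* If VW is truly worse by 0.5, two-sided K-S fails to reject in 100 − 26 = 74% to 100 − 22 = 78% of trials.

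**What an interval would show.** For an unadjusted mean difference the 95% half-width is about 1.96 × 1.5 × √(2/50) = 0.59 at 50 per arm, and 1.96 × 1.5 × √(2/47) = 0.61 at 47.

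**The case against.** A one-sided two-sample K-S test exists, and the text states a one-directional alternative without calling the test two-sided. If that form was meant, the direction problem disappears. This stands: the fault is that the side is not stated, and a reader who infers that the plan cannot test its alternative goes too far. What remains is sensitivity to unequal spread.

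A reader might infer that two rival tests are planned for A1c. The document does not establish this. K-S is attached to A1c by name, and the t-test rule may be meant for the other continuous outcomes. It is an ambiguity, and its cost in type I error is only about 1 to 1.5 points.

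A reader might infer that the plan offers no effect estimate for A1c. That holds for K-S alone. If the t test covers A1c, a mean difference is available, so this complaint and the complaint of competing tests cannot both be pressed in full.

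A reader might infer that K-S is simply the weaker test. That is so for roughly normal changes, but it reverses under heavy tails, and the protocol gives neither the SD nor the shape of A1c changes. The protocol also concedes, under Sample Size and Power Calculations and again in the Discussion, that it is not powered between arms; the t test is poorly powered here too. Low power is therefore not the complaint.

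**Conclusion.** The concern holds in a limited form. A directional question about A1c lowering is tied to a test whose side is unstated, and the usual two-sided form does not separate worse from better (22% to 26% rejection either way) or location from spread (14% to 19% with equal means). A one-sided form repairs the first fault but not the second (15% to 18%). The deciding A1c analysis is not clearly designated.

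These percentages rest on the assumed SD of 1.5, difference of 0.5, SDs of 1.5 and 2.5 in the spread case, normal errors, equal arms and no dropout. The lack of direction in the two-sided test, and the absence of a mean difference from the K-S statistic, do not depend on them.

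Changing the test does not by itself license the claim that VW is at least as good. With no margin stated, non-rejection by any of these tests cannot carry it.

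**What to change.** In Analysis and Statistical Tests, and in the Abstract (Results) to match:

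- Name one A1c analysis: the between-arm difference in mean A1c at 4 months, from a linear model adjusted for baseline A1c, with a 95% confidence interval. Baseline A1c is already measured and used to stratify the randomization.
- Keep the two-sample K-S comparison as a descriptive supplement on the shape of the changes, and say that it does not decide the A1c comparison.
- State which continuous outcomes the t-test rule covers.
- Drop the reading of a non-significant result as showing that VW is at least as good. Report which differences the confidence interval excludes or, if non-inferiority is meant, state a margin in advance and compare the interval with it.

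The cost is wording; no further data are needed. The small downside is that a comparison of means does not test differences in distribution shape, which the supplement would only describe.

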### Qualitative Evaluation

Following completion of the intervention delivery phase, focus groups will be conducted to qualitatively compare the experiences of participants assigned to the VW vs. the face-to-face condition. A total of 40 randomly selected participants will be invited to participate in four focus groups (expecting that 8-10 participants per group will attend): two groups will include VW participants, and the other two will include face-to-face participants. Participants will be consented for participation in, and recording of, the group discussions. We will offer a monetary incentive of US $40 and travel expenses to encourage participation. Two analysts will independently review transcripts of discussions, identifying key words and themes (in vivo coding) related to their experiences of living with diabetes, decision-making about treatments and lifestyle changes, and involvement in the VW or face-to-face intervention. A grounded theory approach will be used [29]. Constant comparative analysis will be used to relate the transcribed focus group interview data through ideas to core concerns. The first approach will involve open coding using a meaningful phrase by meaningful phrase strategy. During the open coding process, data will be coded for any and all categories. Focused codes will be created for sorting and synthesizing the initial codes to organize the data, using the most significant and/or frequent earlier codes to sift through the data. From focused codes, memos will be generated theorizing about how codes relate to ideas and characterizing the emerging theory. Memos will be sorted into concepts demonstrating relationships between concepts that derive from memos. The formulation of themes and codes drawn directly from different sections of the data, and then used to code the transcripts themselves, is a pivotal step toward building an in-depth analysis.

## Discussion

Glycemic control is critical to preventing health disparities in diabetes morbidity and mortality among racial/ethnic minorities such as African Americans. Strategies to maximize access to treatment and self-management support are needed for this and other vulnerable populations. Technology-based interventions may be able to increase access but further evidence is needed to support the feasibility of such interventions with populations that have limited educational and computer literacy. By comparing a VW-based intervention format to a traditional face-to-face format for delivery of a diabetes self-management intervention to a sample of low-income African American women, this study will provide evidence of feasibility for a population with considerable health disparities in diabetes prevalence and outcomes and who also have limited experience with computers.

The strengths of the study are many. They include: (1) assessment of feasibility of utilizing a VW platform for patient health education, (2) randomization of study participants to a face-to-face condition (ie, traditional approach) vs. a VW environment condition, holding constant the intervention content, (3) recruitment of inner city minority participants thus addressing so called digital-divide issues, (4) standardization of hardware used to access the VW, (5) use of a control group that has similar hardware and training, (6) robust measurement of behavioral outcomes, and (7) inclusion of a qualitative post-intervention evaluation.

Limitations of this study include: (1) the pilot nature of the study. Adequately powering a comparative effectiveness study, given the characteristics of our primary outcomes, will require a larger sample size, beyond the scope of this project, and (2) the study focus is on a subset of the population, namely low-income African American women with uncontrolled diabetes. Thus, the generalizability of our findings to men and to non-underserved populations might be limited.

Evidence of feasibility and potential efficacy is needed so that new interventions can be designed for VW implementation and high reach to diverse populations. Our previous work has demonstrated the ability of VW-based training to change the professional behavior of clinicians [30,31]. We anticipate that the current study will produce valuable data and insights to help guide application of these findings to VW-based interventions targeting not only diabetes self-management but also other chronic conditions and health behaviors, including such critical topics as medication adherence, substance abuse cessation and treatment, individual and group-based mental health treatments, many possible rehabilitative services, and other health services.
